### Hypotheses

1a. It is expected that patients’ level of social participation will be higher in the MIP intervention condition compared to the UC after pain rehabilitation treatment and at 6-month follow-up after finishing the rehabilitation treatment.

1b. It is hypothesized that drop-out rates will be lower and adherence to the treatment and the level performing daily activities) will be higher in the MIP condition compared to the UC.

2. It is hypothesized that MIP will be more efficient compared to UC, both in effects as well as utilities.

3. It is hypothesized that the MIP intervention is feasible for the participating nurses and the MI fidelity of the MIP intervention is sufficient.

## Methods/Design

### Study design

The PREPARE study is a parallel single-blind RCT.

### Recruitment

Participants will be recruited from the outpatient department of Rehabilitation Medicine in an academic and a regional hospital in the Southern part of the Netherlands, starting in January 2012 and lasting till June 2013.

Patients visiting one of the participating outpatient rehabilitation departments for an intake interview will be evaluated whether they are eligible for rehabilitation treatment by the consultant in rehabilitation medicine.

### Participants

Participants are patients who meet the inclusion criteria as stated below.

In current care, patients are selected for rehabilitation treatment by the consultant in rehabilitation medicine based on expert opinion. For this, both medical (origin and severity of the pain problem and interfering co-morbidity) and motivational factors are evaluated. In patients eligible for outpatient pain rehabilitation treatment, additional inclusion and exclusion criteria for participation in the PREPARE study are checked and in case of eligibility, patients will be invited to participate.

Inclusion criteria are: non-specific chronic (duration >3 months) musculoskeletal pain; age between 18 and 65 years; the chronic pain syndrome is not attributable to a recognizable, known specific pathology (for example, infection, tumor, osteoporosis, fracture, structural deformity, inflammatory disorder (for example, ankylosing spondylitis); medium to high level of motivation for pain rehabilitation from the consultant’s perspective; adequate literacy to complete assessment measures.

Exclusion criteria: pregnancy; surgery planned in the foreseeable future; patient involved in litigation procedures; suspicion of a psychiatric disease that will interfere with rehabilitation treatment (according the expert opinion of the consultant in rehabilitation medicine).

### Sample size

The sample size calculation is based upon an estimated difference in change in level of participation between baseline and 6-month follow-up (after completion of the rehabilitation treatment) as assessed by the Utrecht Scale for Evaluation of Rehabilitation-Participation (USER-P) [35,36]. Reproducibility [37], responsiveness [38], and validity [37] of the USER-P are satisfactory. As participation is the important outcome in rehabilitation, we have chosen this as primary outcome. The scale consists of the three aspects of participation represented by the subscales Frequency, Restriction, and Satisfaction. The sum score of each subscale is converted to scores on a scale ranging from 0 to 100. There is no USER-P total score.

Our sample-size calculation is based upon the subscale Satisfaction. This subscale is the most important part of participation as it marks the subjective experience of participation [9]; therefore we have chosen this one.

As at this moment no information is available about the USER-P in a pain population regarding normative values, clinically relevant change, and clinically relevant difference, our study is exploratory of character. In a study by van der Zee (2011) the USER-P is taken in different patient groups at three different points in time [38]. As these groups were part of a cohort study, nothing is known about differences after a specific treatment. We know from other studies that multidisciplinary pain rehabilitation treatment is moderately effective with effect sizes ranging from 0.30 for behavioral outcomes up to 0.40 for functional outcomes [14]. We expect an additional effect for the MIP intervention since systematic reviews of motivational interviewing-based interventions show an effect size ranging from 0.27 up to 0.40 when compared with a weak comparison group [30-32,39]. It has to be said that in those reviews no study in the field of chronic pain or rehabilitation treatment was taken into account. Therefore, our power calculation is based on the following two assumptions:

1. Using an expected mean change of 5 points within UC is expected whereas a difference of additional 5 points (thus at least 10 points in total) within MIP in the USER-P sub scale Satisfaction is considered as clinically relevant. Those numbers are estimates as the clinically relevant difference is not known yet.

2. Assuming a standard deviation of 10 points in both groups, the standardized effect size, Cohen’s d, is (10–5)/10 = 0.5 indicating a medium additional effect size of the MIP [40].

Assuming power (1-β) of 80%, α = 0.05, two-sided testing, and holding the above mentioned assumptions, would necessitate *n* = 128 participants (*n* = 64 per arm). With an expected total drop-out of 20% (10% drop-out from the study, another 10% drop-out during the usual rehabilitation treatment as our unsystematic registration has shown), *n* = 160 (*n* = 80 per arm) was chosen as the optimal total sample size. Additionally, as the recruitment of 160 participants in the region of South-Limburg/the Netherlands is feasible in a time range of 18 months, we have chosen for this amount of participants.

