Unfortunately, in the current rehabilitation care, non-adherence and drop-out are major problems. Adherence rates are low in patients with chronic conditions [17], and subsequently, drop-out of pain rehabilitation programmes, ranging from 9% to 42%, is high [18-20]. Previous research showed that adherence and non-drop-out of treatment is related to a better outcome in physical and emotional functioning and pain severity [21]. Adherence is influenced by multiple factors such as the healthcare provider-patient relationship, the patient’s self-efficacy to be able to make changes [22], and the patient’s satisfaction with improvement [23].

In order to improve adherence and motivation to prevent drop-out, and to strengthen self-efficacy, motivational interviewing (MI) has been proposed [24]. Miller and Rollnick, the founders of MI, defined it as ‘directive, client-centred counselling style for eliciting behaviour change by helping clients to explore and resolve ambivalence’ [25]. The overall goal is to increase the client’s intrinsic motivation to change and enhance behavioral change [26]. MI was originally developed for problem drinkers [27] and in the beginning applied in the addiction field only (for example, [28,29]). Meta-analyses showed that using MI as a pre-treatment yielded the best outcomes compared with other active treatments [30-32]. Therein, MI was designed to prepare clients for further treatment such as CBT or an inpatient program. Furthermore, the effective application ranged from a variety of disorders such as addiction (except smoking cessation), increasing healthy behaviors, and the management of chronic illnesses. MI as treatment approach is fairly new in the field of chronic pain. MI has been applied with promising results in two small randomized controlled trials (RCTs) within primary care for patients with chronic pain conditions. Habib *et al*. [33] found significant increases in attending self-management workshops after a psychologist-led two-session MI-based feedback interview compared with an attention placebo interview [33]. Another recent study found a MI-adapted intervention added to outpatient physiotherapy for patients with back pain effective in enhancing motivation and exercise adherence compared to physiotherapy alone [34].

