### Data collection

For the (cost-) effectiveness evaluation, measurements will be carried out before the first MIP/UC pre-treatment sessions (T0), after the MIP/UC (T1 = post pre-treatment), after the regular multidisciplinary pre-rehabilitation assessment (before starting rehabilitation), at the start of the pain rehabilitation treatment (T2), after treatment completion (T3), and at 6-month follow-up (T4). Study assessments at T0, T2, and T3 will be integrated in current care clinical assessment battery pre-rehabilitation and post rehabilitation (see also Figure 1 (flow-chart) and Table 2). Cost measurements will be carried out at three points: T0, T2, and T4. Information on drop-out from and adherence to the (pre-) rehabilitation treatment, start and end date of the treatment, and no show are derived from the administrative patient registry.

**Table 2 T2:** Outcome measures, abbreviation instrument, and assessment moments PREPARE study

		**Baseline**	**Two sessions**	**After pre-treatment**	**Start pain rehab treatment**	**Finish pain rehab treatment**	**6 months after T3**
	**Abbr.**	**T0**^**a**^		**T1**	**T2**^**a**^	**T3**^**a**^	**T4**

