#### Process evaluation in participants and nurses

A process evaluation is needed to evaluate the actual delivery of our pre-treatment intervention, the process evaluation focuses on the level of nurses and patients [101].

1. Patients: Patients will be asked to score their satisfaction with pre-treatment in a set of questions for process evaluation purposes at the end of the pre-treatment intervention (included in the questionnaire of T1). In case of treatment drop-out, a patient is asked to answer the questions regarding satisfaction with the (pre-) treatment directly after the decision to stop, including reasons for drop-out from treatment.

Furthermore, client-centeredness will be assessed by the Client Centred Care Questionnaire (CCCQ). The questionnaire was originally developed for the use in clients receiving homecare [102]. By making some minor revisions, it can also be used in the rehabilitation setting [103]. It has shown good psychometric qualities [102].

2. Nurses: After both pre-treatment sessions, nurses are asked to fill in a short questionnaire. Questions are asked about the steps taken during the intervention, the content of the discussion during the sessions, and the client’s active participation. The questionnaire’s structure is based on the work of Steckler and Linnan [101] and adapted to the specific situation of our study.

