#### Effect evaluation

Baseline data will be analyzed to describe the characteristics of all participants and to check for significant imbalances between the two groups. Possible baseline differences between the intervention group and the control group will be tested by an independent samples *t*-test (normal distribution) or Mann–Whitney U tests (non-normal distribution) in the case of continuous variables. In the case of dichotomous variables, a Chi-square test will be used. In case of imbalances in prognostic factors between both randomized groups, an adjustment for those factors will take place. The number of drop-outs and follow-up losses in both groups will be reported based on descriptive data. Differences in primary and secondary outcome measures between MIP and UC will be analyzed using repeated measurements techniques and multilevel analysis. This approach is chosen because repeated measures within individual subjects are taken. A *P* value <0.05 is considered statistically significant. Data will be analyzed according to the intention-to-treat principle. All outcomes will be assessed at each follow-up moment by taking into account a specific a priori hypothesis. Additionally, per protocol analyses will be performed to assess whether protocol deviations have caused bias.

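### The primary time point is dated from completing rehabilitation, and the sample size counts rehabilitation drop-outs as lost, which does not fit the stated intention-to-treat analysis

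*Protocol article*

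**What the plan says.** Under Primary outcome, the endpoint is the between-arm difference in USER-P change from T0 to T4. Data collection places the last two assessments "after treatment completion (T3), and at 6-month follow-up (T4"). Table 2 labels T3 as the finish of rehabilitation and T4 as six months after T3; the abstract and the Sample size section use the same anchor. Table 2 schedules the USER-P at T0, T1, T3 and T4, not at T2.

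The Sample size section derives 64 per arm and raises this to 80 for a 20% loss made up of "10% drop-out from the study, another 10% drop-out during the usual rehabilitation treatment as our unsystematic registration has shown".

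Effect evaluation states: "Data will be analyzed according to the intention-to-treat principle". It adds per-protocol analyses and names repeated-measures and multilevel methods.

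For someone who stops treatment, the contact described is in the process evaluation, where "a patient is asked to answer the questions regarding satisfaction with the (pre-) treatment directly after the decision to stop", together with the reasons for stopping.

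The Aims and hypothesis 1b make lower drop-out something MIP is expected to achieve on the way to better participation. The Background says that "drop-out of pain rehabilitation programmes, ranging from 9% to 42%, is high".

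**The concern.** An intention-to-treat comparison at T4 needs a T4 value, or at least a T4 date, for everyone randomised. Here the date depends on an event after randomisation, finishing rehabilitation, which some patients will not reach. The sample size is built as if those patients yield no primary outcome. The article's allowance for varying waiting time and treatment length does not cover non-completion.

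This matters more here than in most trials because drop-out is what the intervention targets. If hypothesis 1b is right, fewer T4 values will be missing under MIP than under UC. The Background also links staying in treatment to better outcome, so the missing values would not be a random subset. A patient without T3 and T4 has no USER-P later than T1, that is, none after rehabilitation begins. The model would then have to project that patient's T4 from two pre-rehabilitation scores and the course of patients who stayed.

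**Working it through.** **Inputs from the Sample size section.** "α = 0.05, two-sided testing"; "Assuming power (1-β) of 80"%; "a difference of additional 5 points (thus at least 10 points in total) within MIP", against 5 points under UC, so a 5-point difference; SD 10; equal arms; attrition 10% + 10%.

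**1. The plan's own figure.** Normal approximation: n = 2 × (1.960 + 0.842)² × 10²/5² = 62.8, so 63 per arm. The two-sample t-test gives 63.8, so 64 per arm, with power 0.801. Inflation: 64/0.80 = 80 per arm, 160 in total. Applying the two losses in sequence, 64/(0.90 × 0.90) = 79.01, also rounds up to 80. The stated figures reproduce.

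**2. What the second 10% does.** With study loss only, 64/0.90 = 71.1, so 72 per arm, 144 in total. The step from 144 to 160 comes from treating rehabilitation drop-outs as non-evaluable.

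**3. Size of the retention component.** Let drop-out be pU under UC and pM under MIP. Let completers gain C under UC and C + e under MIP, and drop-outs gain D in either arm. Then:

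- intention-to-treat difference = (1 − pM) × e + (pU − pM) × (C − D)
- difference among completers = e

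The second term of the first line is the retention part; a comparison resting on completers does not contain it. The documents give neither C − D nor pM. Assuming a gap C − D of 5 to 10 points:

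| pU vs pM | Retention part (points) | Share of 5 points |
|---|---|---|
| 10% vs 5% | 0.25 to 0.5 | 5% to 10% |
| 10% vs 0% | 0.5 to 1.0 | 10% to 20% |
| 42% vs 21% | 1.05 to 2.1 | 21% to 42% |

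The first two rows use the plan's 10%; the third starts from the top of the range in the Background. Completers also count e in full, where intention-to-treat counts (1 − pM) × e, so the net direction of the distortion is not fixed in advance.

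**4. Power if drop-outs are followed and analysed.** With 80 randomised per arm and 10% study loss, 80 × 0.90 = 72 per arm are evaluable (two-sample t-test):

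| Difference in the whole population | Power |
|---|---|
| 5 points | 0.846 |
| 4.75 points | 0.808 |
| 4.5 points | 0.765 |
| 4.0 points | 0.664 |

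The 4.5 figure assumes that 10% of those analysed show no difference between arms (0.90 × 5). The 4.75 figure would follow if they showed half of it (0.90 × 5 + 0.10 × 2.5). Holding 80% power at 4.5 points needs 79 evaluable per arm, so 79/0.90 = 87.8, or 88 randomised per arm (176 in total).

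**The case against.** The strongest reply is that an attrition allowance is not an analysis rule. The article nowhere excludes drop-outs. It declares intention-to-treat, reports treatment drop-outs and follow-up losses as separate items, and adds a per-protocol analysis that would have little purpose if the main one were already restricted to completers. Inflating for expected missing outcomes is compatible with intention-to-treat. The registry records treatment end dates, so an early stopper may have a date from which to count. A multilevel model keeps the T0 and T1 scores. The drop-out questions belong to the process evaluation and do not say that outcome collection ceases. Drop-out is itself compared between arms.

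Most of this stands, and it limits the point. A reader might infer that the primary analysis is completers against completers; the documents do not say so. A reader might also infer that the effect of MIP would vanish or change sign. That requires assumed gains, and in particular no effect among completers, for which the article gives no basis. Nor does the article support reading the power as collapsed. Combining 42% rehabilitation loss with 10% study loss leaves about 38 per arm and power 0.58 (160 × 0.48/2 = 38.4), or about 42 per arm and 0.62 if the losses are taken in sequence (80 × 0.90 × 0.58 = 41.8). But 42% is the top of a cited range for other programmes, not the planning figure.

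The reply does not remove the mismatch. The anchor and the allowance are positive statements, not details left to a fuller document, and both point towards having no T4 for patients whom the analysis principle requires. An end date in a registry is not a rule for dating T3 and T4, and never-starters have none. T0 and T1 scores cannot show what happened after rehabilitation was abandoned.

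**Conclusion.** The point holds as an inconsistency between the timing of the primary endpoint, the attrition assumption and the analysis principle. T4 is undefined for never-starters and ambiguous for early stoppers, and the move from 144 to 160 relies on drop-outs giving no primary outcome. Followed literally, this leaves missing T4 data that are probably related to outcome and possibly unequal between arms.

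At the planned drop-out rate the consequence is moderate: about 0.25 to 1.0 of the 5 points, under the assumed gain gap and MIP drop-out of 5% to 0%, and more if drop-out is higher. The 64 and 80 per arm are correct for the assumptions stated. If drop-outs are followed, 160 patients still give more than 80% power down to about 4.75 points. The weakness lies in who is counted and when they are measured, not in the calculation.

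**What to change.** State that every randomised patient is assessed with the USER-P at T3 and T4 whatever their rehabilitation status. Set those dates for patients who stop or never start, for example from the planned end of their rehabilitation, or at a fixed interval from randomisation where no end was planned, with T4 six months after T3. Include these patients in the primary intention-to-treat analysis. For those who have already stopped, collect T4 at the equivalent date while that is still possible.

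Base the attrition allowance on missing outcomes only, set the target difference for the whole randomised population, and report power on that basis, as in step 4 of the working.

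The cost is follow-up questionnaires for about 16 patients (10% of 160), plus any who never start, and a power figure that may be less favourable. The article does not say how T4 is administered, so whether extra visits are needed cannot be judged from it. The change should be made while patients are still in follow-up, because T4 data not collected on time cannot be recovered.

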### Informed consent, randomization, and blinding

Standard informed consent procedures will be used. After having received informed consent, the participants are randomly assigned to either the experimental intervention condition (MIP) or the control condition (UC). Block randomization with block size of four are used per study site (hospital) to obtain equal numbers in both arms. An independent research assistant will execute the randomization by means of a computerized random number generator resulting in a computer-generated list of random numbers to allocate the participant either to the experimental or the control condition. The consultant in rehabilitation medicine, the rehabilitation team and the participant will all be blind for the result of the allocation to the UC or the MIP but not for participation in the study at all. The research assistant responsible for the logistics of the present study and the participating nurses administering the intervention and control condition are not part of the treatment team and are not blinded for allocation.

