#### Nurses

Both UC and MIP are administered by registered nurses working in the field of rehabilitation. In order to prevent contamination of treatment by components of the other intervention, nurses will be trained and only guide participants in one specific condition. The two nurses selected to deliver the MI condition, are both experienced MI coaches (4 years of experience). To assure optimal quality of the MI condition, both nurses receive an expert training by a certified MI trainer: their MI knowledge and experience in the context of chronic pain rehabilitation are updated based on an evidence-based training tailored to their specific needs [45-49]. During the study the MI sessions will also be audio taped and the MI quality will be assessed using a coding instrument (Motivational Interviewing Treatment Integrity (MITI)) (see also Methods section, Process evaluation section). Subsequent training will be based on additionally regular supervision, done by training on the job and direct feedback on MIP sessions.

Quality of the UC condition:

The two nurses selected to deliver the usual care condition are experienced in the field of rehabilitation (20 years and 5 years, respectively).

Before the start of the study, they will receive a 3-h refresher training in general communication skills and general principles of health education. In addition, the content of relevant chapters of the book ‘Mastering pain’ is discussed. During the study, the nurses of the UC condition will meet once or twice a year to discuss problems encountered during the sessions.

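### A fixed, published block size of four per hospital makes up to a third of allocations certain to unblinded staff, and hospital should be named as a model term

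*Protocol article*

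**What the plan says.** **Allocation.** Under *Informed consent, randomization, and blinding* the protocol article states: "Block randomization with block size of four are used per study site (hospital) to obtain equal numbers in both arms". There are two strata, because patients come from outpatient departments "in an academic and a regional hospital in the Southern part of the Netherlands". An independent research assistant allocates from a computer-generated list after consent. The consultant, the rehabilitation team and the participant are declared blind. The logistics assistant and the nurses "are not part of the treatment team and are not blinded for allocation".

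**Who sees whom.** Under *Nurses*, two nurses serve each arm, and "nurses will be trained and only guide participants in one specific condition". Under *Participants*, the consultant decides on entry, and one inclusion criterion is "medium to high level of motivation for pain rehabilitation from the consultant’s perspective".

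**Timing.** Recruitment was planned from January 2012 to June 2013 (*Recruitment*, *Trial status*). The article appeared on 2 April 2013.

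**Analysis.** *Effect evaluation* names repeated-measures techniques and multilevel analysis. The reason given is: "This approach is chosen because repeated measures within individual subjects are taken". It adds that prognostic factors found to be imbalanced between arms will be adjusted for. It gives no list of model terms and mentions hospital neither as included nor as excluded.

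**The concern.** A constant block size lets anyone who knows it and the arms already assigned work out the end of each block. Three features of this trial make that worth attention:

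- Each nurse delivers one condition only, so learning which nurse saw a patient reveals that patient's arm.
- Entry depends partly on a subjective rating of motivation, which is what the intervention targets.
- The primary outcome is self-reported.

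If knowledge of coming allocations reached the person deciding on entry, patients with better or worse prospects could be steered towards one arm, and no later analysis could fully undo that.

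The second matter is smaller. Randomisation is stratified by hospital, so the analysis should reflect hospital. An adjustment rule triggered by observed imbalance is a poor route to that, because stratification is meant to prevent imbalance on exactly this factor. What is at stake here is precision.

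**Working it through.** **The plan's own figures.** The article gives no figure for predictability. Its sample size does reproduce. The inputs are a 5-point difference, an SD of 10 (so d = 0.5), and "Assuming power (1-β) of 80%, α = 0.05, two-sided testing". The two-sample t-test needs 63.77, rounded up to 64 per arm, or 128 in total, with power 80.1%. Allowing for 20% drop-out, 128 / 0.80 = 160.

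**Forced allocations with blocks of four.** At 1:1 each block holds two of each arm, giving six equally likely orders. A position is forced once one arm is used up.

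- AABB and BBAA: positions 3 and 4 are forced, 2 each, total 4.
- ABAB, ABBA, BAAB and BABA: position 4 is forced, 1 each, total 4.
- Together: 8 / 24 = 33.3%, or 160 × 1/3 ≈ 53 patients, counting complete blocks.

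**Best guess with full knowledge of earlier arms.** The chances of a correct guess are:

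- position 1: 1/2
- position 2: 2/3
- position 3: 1/3 × 1 + 2/3 × 1/2 = 2/3
- position 4: 1

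The mean is (0.500 + 0.667 + 0.667 + 1) / 4 = 70.8%, against 50% under simple randomisation.

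**Randomly varying sizes.** These were simulated with 80 allocations per hospital (an assumed even split) and an observer who knows the set of sizes but not their order.

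| Block sizes | Certain | Best guess correct |
|---|---|---|
| 4 (enumerated) | 33.3% | 70.8% |
| 4, 6 | 5.5% | 69.2% |
| 2, 4, 6 | 4.1% | 70.1% |
| 4, 6, 8 | 2.4% | 67.8% |

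Certainty nearly disappears; general predictability hardly moves.

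**Exposure created by publication.** About 15 of the 18 recruitment months had passed by 2 April 2013. If accrual was even (an assumption), 160 × 3/18 ≈ 27 patients remained, of whom 27 / 3 = 9 would have certain allocations.

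**Hospital in the model.** If hospital explains a share R² of outcome variance and is balanced across arms, adjusting for it multiplies the standard error by √(1 − R²). The documents give no R², so 2% to 10% is an assumed range.

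- R² = 0.02: √0.98 = 0.990, about 1% smaller.
- R² = 0.10: √0.90 = 0.949, about 5% smaller.

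A simulation with 64 per arm, two equal hospitals, d = 0.5 and the SD of 10 taken as the within-hospital SD gives:

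| Assumed hospital difference | Type I error, hospital omitted / included | Power, hospital omitted / included |
|---|---|---|
| 0.25 SD | 4.7% / 4.9% | 79.6% / 80.0% |
| 0.5 SD | 4.1% / 4.7% | 78.3% / 80.0% |
| 1 SD | 2.9% / 4.9% | 72.6% / 79.8% |

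Omitting hospital makes the test conservative and costs some power. It does not raise the false-positive rate. If 10 points is already the total SD, including hospital is a gain over the planned power rather than the recovery of a loss.

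**The case against.** The main defence is the separation of roles in the same section as the block size. The consultant who rates motivation is blind, allocation follows consent and is carried out by an independent assistant, and the staff who know the arms are outside the treatment team and are not described as selecting patients. A nurse directly sees only patients of her own arm, so even she would need to know how many others had been randomised in between. A reader might infer that a third of allocations are predictable to the person recruiting, or that selection bias is likely. The documents do not support that, and 53 of 160 is a ceiling that assumes full leakage at both hospitals. This part of the objection stands.

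It does not dispose of the point. Concealment then rests on staff discretion alone, in a design where the nurse's identity gives away the arm. The article also does not say whether the independent assistant and the unblinded logistics assistant are different people.

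Two further objections stand. Publication came late, so it exposed only the last part of recruitment. And varying the block sizes leaves best-guess success near 70%, so the remedy removes certainty rather than predictability.

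On the second matter, a reader might infer that hospital has been left out of the analysis model. The article lists no model terms, multilevel analysis leaves room for a hospital term, and an analysis plan that is not shown may include one. Silence is not exclusion. What stands is narrower: hospital is not named, and the one adjustment rule that is stated would tend to pass over it.

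**Conclusion.** The point holds in limited form. The block scheme makes up to one third of allocations certain (at most about 53 of 160) to someone who knows the block size and every earlier arm at that hospital. By the article's own account that could only be the unblinded nurses and the logistics assistant. Bias in patient selection would require information to leak to the consultant, or unblinded staff to influence enrolment. The document describes neither and gives no basis for quantifying either, so this is an avoidable weakness in concealment and not evidence of bias.

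For hospital, the article does not commit to analysing by the stratification factor. The consequence is modest: a standard error about 1–5% smaller with the term than without it, on an assumed R² of 2–10%. At an assumed 0.5 SD hospital difference, less than 2 percentage points of power are at stake. A reader might take the missing term as a source of bias; with hospital balanced across arms by design, omission gives conservative inference instead.

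**What to change.** **Allocation.** For any blocks not yet generated, draw block sizes at random within each hospital (for example 2, 4 and 6, or 4 and 6), let only the independent assistant hold the list, and disclose the sizes only after recruitment closes. State whether that assistant is separate from the logistics assistant. If the list is already complete, report the fixed, published block size as a limitation, together with who knew the allocations.

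The cost is a new list for the remaining blocks and a slightly larger possible imbalance at the end. An unfinished block of four can leave the arms 2 apart per hospital, and a block of six can leave them 3 apart. Over two hospitals that is at most 6 instead of 4.

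**Analysis.** State that hospital, as the stratification factor, enters the primary and secondary outcome models as a fixed factor whatever the observed balance. With two hospitals this costs one parameter.
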